## Abstract

**Introduction:**

Pressure continues to grow on emergency departments in the UK and throughout the world, with declining performance and adverse effects on patient outcome, safety and experience. One proposed solution is to locate general practitioners to work in or alongside the emergency department (GPED). Several GPED models have been introduced, however, evidence of effectiveness is weak. This study aims to evaluate the impact of GPED on patient care, the primary care and acute hospital team and the wider urgent care system.

**Methods and analysis:**

The study will be divided into three work packages (WPs). WP-A; Mapping and Taxonomy: mapping, description and classification of current models of GPED in all emergency departments in England and interviews with key informants to examine the hypotheses that underpin GPED. WP-B; Quantitative Analysis of National Data: measurement of the effectiveness, costs and consequences of the GPED models identified in WP-A, compared with a no-GPED model, using retrospective analysis of Hospital Episode Statistics Data. WP-C; Case Studies: detailed case studies of different GPED models using a mixture of qualitative and quantitative methods including: non-participant observation of clinical care, semistructured interviews with staff, patients and carers; workforce surveys with emergency department staff and analysis of available local routinely collected hospital data. Prospective case study sites will be identified by completing telephone interviews with sites awarded capital funding by the UK government to implement GPED initiatives. The study has a strong patient and public involvement group that has contributed to study design and materials, and which will be closely involved in data interpretation and dissemination.

**Ethics and dissemination:**

The study has been approved by the National Health Service East Midlands—Leicester South Research Ethics Committee: 17/EM/0312. The results of the study will be disseminated through peer-reviewed journals, conferences and a planned programme of knowledge mobilisation.

**Trial registration number:**

ISRCTN51780222.

Strengths and limitations of this studyWe will disseminate a comprehensive assessment of general practitioners and emergency departments (GPED) from multiple perspectives to identify models of care which are likely to be most efficient, to maximise clinical and cost-effectiveness, to reduce staff pressure and to improve patient outcome and safety.Retrospective analysis of nationally available data and the associated economic analysis will be constrained by the quantity and quality of the available information.The mixed-methods approach will allow us to elucidate the aims of GPED, the underlying assumptions about how these aims will be achieved and to assess impacts while considering local context.The mixed-methods analysis will also enable the development of recommendations to improve future implementation by identifying challenges and potential solutions.GPED models are likely to show significant variation both within and between hospital sites; this may present a challenge to generalisability.

## Introduction

Despite many initiatives to reduce demand, pressure from rising attendance rates continues to grow on emergency departments in the UK, with an associated decrease in performance.^1^ This leads to emergency department crowding, associated with adverse outcomes and increased mortality.^2 3^ There is a clear need to find solutions that reduce the burden on emergency departments and improve patient experience and safety. In England, the ‘Keogh Review’ of urgent and emergency care aims to reduce pressure on emergency departments by treating more patients close to home in primary and community settings.^4^ It includes a recommendation that colocated primary care models should be considered in every emergency department,^5^ however, the optimal model to achieve this has not yet been identified, and evidence for the effectiveness of general practitioners in the emergency department (GPED) is weak both in the UK and internationally.^6–9^ A recent review of primary care services located with emergency departments concluded that there is very little evidence to support this model of care, and that ‘a robust evaluation… is needed to inform future policy’.^10^

Nevertheless, there is an increasing trend to include general practitioners at the hospital front door. A joint report from four Medical Royal Colleges recommended that every emergency department should have a colocated primary care facility.^11^ Estimates of the proportion of emergency department patients that could be managed by a general practitioner vary widely between 15% and 40%.^4 12^ There are a range of models of integration; most involve general practitioner services alongside emergency department staff, with some operating a separate colocated service as a primary care ‘filter’ in front of the emergency department, while others are more integrated with the emergency department team. A three-part taxonomy proposed by the Primary Care Foundation^6^ describes three main operational models: a general practitioner service located alongside or next to the emergency department; general practitioners working at the front of the department screening attendees and either treating or diverting to other places—effectively acting as a filter; general practitioner services fully integrated into a joint operation covering the whole range of primary care and emergency services. Recent evidence suggests that some form of colocation exists in 43% of emergency departments,^13^ however, this is likely to have increased rapidly as a result of policy initiatives to increase colocation, including a capital investment of £100 million made by the UK government in March 2017.^14^

There is also a lack of clarity about the hypothesised mechanism through which locating GPED will reduce pressure on these departments. While it has been suggested that implementing a GPED may have some benefits for patients, the consequences for the healthcare workforce, both general practitioners and hospital staff, have not been studied, particularly when there is real uncertainty as to whether GPED reduces emergency department attendances^15^ and/or emergency admissions.^16^ Some of the apparent impact of GPED on emergency departments may simply be relabelling of the same work, with no real benefits for patients or the National Health Service (NHS). Colocated general practitioner services may further increase demand at hospital sites, transferring the problem of overcrowding from one location to another. In particular, it is not clear what the impact is for general practitioners, who are already overstretched and in short supply, and GPED may not be the best use of their time and skills.^17^ Finally, the cost of implementing and running GPED is a legitimate concern, since employing general practitioners is likely to be more expensive than employing other types of staff.^18^ Although GPED may be effective in reducing emergency admissions, they may not be cost-effective.^9^

For patients as service users, expectations and regard for their care and experience are important considerations. Research indicates that patients may attend the emergency department with non-urgent health problems because of the ease of access or a perceived need for diagnostic tests.^19^ Attendances at emergency departments are a small proportion of all urgent care consultations when compared with general practitioner surgeries in the surrounding area, so small shifts in patient behaviour away from general practice could have major implications for the demand on emergency departments.^20^

Effective evaluation of the different models of GPED, including various approaches to patient triage and streaming, and the extent of integration with existing emergency department services, is essential to inform service development and meet the urgent heath needs of the population. As a result, this issue will remain highly relevant and important to the future needs of healthcare systems. There is a lack of clarity about the intended benefits and mechanisms of GPED, and little evidence to underpin existing hypotheses.

## Research question

What is the impact of GPED on patient care, the primary care and acute hospital team and the wider urgent care system? What is the differential impact of alternative models of GPED?

The study will use a mixed-methods approach, divided into three work packages (WPs) (figure 1).

**Figure 1 F1:**
[figure not shown]
Study flow diagram. A&E, accident and emergency; HES, Hospital Episode Statistics; WP, work package.

This study is an investigation of complex processes and systems and requires the use of both quantitative and qualitative data. Quantitative methods will be used in WP-B to address research questions about causality, effectiveness, costs and consequences. Qualitative methods will be used in WP-A and WP-C to develop in-depth insight into the main models of GPED care; this will include understanding the aims of introducing GPED and the expected outcomes. These hypotheses will vary according to the context of the service being introduced.

This approach draws on the strengths of both quantitative and qualitative paradigms. Qualitative data will enable us to describe the current range of models and the mechanisms by which they operate, and to understand the intended aims of the policy. Quantitative data will allow us to test whether the aims have been achieved, while the synergies arising from a mixed-methods approach to data analysis and interpretation will enable us to explore in depth how and why GPED did or did not work in the way intended in different contexts. This will enable us to make meaningful comparisons across sites and for different models of GPED.

## Methods and analysis

See table 1 for a summary of research objectives, WPs and methods.

**Table 1 T1:** Research objectives, work packages (WPs) and methods

Research objectives	WPs	Methods
1. To map and describe current models of (general practitioners and emergency departments) GPED in England.	WP-A	System leader interviews and documentary analysis.
2. To determine the impact of GPED on patient processes and outcomes including overall attendances, attendances in different components of the local urgent care system, waiting times, emergency admissions, reattendances and mortality.	WP-B WP-C	Retrospective analysis of Hospital Episode Statistics data. Analysis of local data and non-participant observation.
3. To assess the impact of GPED on the casemix of admitted patients by exploring admission rates, including the number and proportion of short stay and zero-day admissions, subject to an examination of coding behaviour by hospital trusts, and any changes that may undermine the reliability of this measure.	WP-B	Retrospective analysis of Hospital Episode Statistics data.
4. To explore the impact of GPED on general practitioners, including turnover, absence, satisfaction, well-being and attitudes to and scope of practice.	WP-C	Mixed-methods approach including workforce surveys and interviews.
5. To explore the impact of GPED on the working patterns and roles of other healthcare professionals in the emergency department, including training, workload, skill mix and expertise.	WP-C	Mixed-methods approach including workforce surveys and interviews.
6. To explore the impact of GPED on local urgent care services, on the wider system including primary care (eg, demand for in-hours and out-of-hours general practitioner appointments), and on the interface between services including patient flow.	WP-C	Mixed-methods approach using secondary data analysis and qualitative techniques.
7. To assess the impact of GPED on patients and carers.	WP-C	Interviews and non-participant observation.
8. To compare resource utilisation and costs of care at emergency department sites with and without GPED, and to compare the costs of different service models.	WP-B	Economic analysis.
9. To prospectively evaluate the current promotion of GPED models of care through collaboration with sites that have bid for capital funding to implement GPED, conducting interviews with identified system leaders and measuring changes in the above parameters over time and as implementation occurs.	WP-C	Prospective mixed-methods case study approach.

### WP-A: mapping and taxonomy

We will map, describe and classify current models of GPED in all emergency departments in England and examine the hypotheses that underpin GPED and its anticipated benefits.

We will work with the Royal College of Emergency Medicine and NHS England to identify, describe and classify current models of general practitioner working in all emergency departments in England, exploring the nature of these colocations, current service configuration, local funding arrangements and the date of commencement of any service change(s). We will triangulate these sources with Care Quality Commission data, direct enquiry to individual sites and relevant data available from other researchers with an interest in this subject area to understand and classify current models of care, building on the three-part taxonomy proposed by the Primary Care Foundation.^6^

We will rank the identified models of care in order of frequency, and anticipate that two or three distinct model types are likely to emerge which we can then describe and examine in more detail through WP-B and WP-C. Work will also be carried out to establish the hypotheses that underpin GPED. We will approach senior clinicians and managers in selected national organisations including NHS England and the Department of Health, inviting them to participate in a semistructured interview that will explore their views on GPED and the potential advantages and disadvantages of this service configuration. We will conduct approximately 10–12 interviews that will be recorded digitally, transcribed verbatim and analysed thematically to identify anticipated benefits and impacts of the main GPED models.

### WP-B: quantitative analysis of national data

We will measure the impact of the GPED models identified in WP-A, compared with a no-GPED model, using retrospective analysis of Hospital Episode Statistics data. We will adopt a quasi-experimental approach using a repeated interrupted time series design and estimate difference-in-difference regression models with closely matched non-GPED sites as controls. A cost-effectiveness analysis will also be conducted on different GPED models based on their estimated effects alongside resource use.

In this WP, we will conduct a quantitative analysis of administrative data to measure the effectiveness, costs and consequences of the most prevalent models of GPED being implemented in hospitals in England.

#### Methods

We will analyse emergency department attendance data, Hospital Episode Statistics inpatient data and Hospital Episode Statistics Accident and Emergency data for the period 2010–2011 to 2015–2016. This analysis will be extended to later periods as more data become available during the lifetime of the project. These data will be gathered to address the primary and secondary outcomes of WP-B, which are listed in box 1.Box 1Summary of primary and secondary outcomes for WP-BPrimary outcomeNumber of emergency department attendances.Secondary outcomes4-hour performance.Unplanned emergency department reattendance within 7 days.Patients leaving the emergency department without being seen.Mortality within 28 days of attendance.Emergency hospital admission.Zero-day admission (subject to an examination of coding behaviour by hospital trusts).WP, work package.

National data will be used unless there are specific reasons to exclude individual hospitals, for instance, on the grounds of data quality. There is no sampling for this WP, therefore, a sample size calculation is not appropriate.

This WP will also include costs and consequences calculations of different GPED models based on their estimated effects on the outcomes listed in box 1 alongside estimated resource use (eg, general practitioner salaries, incremental change in other staffing levels and costs), all derived from routine administrative datasets and local datasets (WP-C) supplemented by information from WP-A. We will use Personal Social Service Research Unit cost estimates supplemented by local cost estimates to value changes in activity and resource inputs. We will use information on the most common funding arrangements for GPED (from WP-A) to differentiate between costs that fall on hospital and primary care budgets, with the objective of identifying genuine changes in resource utilisation rather than cost shifting.

#### Analysis

We will adopt a quasi-experimental approach, using a combination of interrupted time series and difference-in-difference regression models to identify the causal effect of each GPED model on the primary and secondary WP-B outcomes. We will initially pool all hospitals and GPED types to identify levels and trends before and after implementation, using a multilevel approach. Trends in each hospital and subgroup (based on date of service introduction) will be examined. We will also conduct stratified analysis by GPED model and by early/late adopter status to determine whether there are differences in effects, and as such which model of GPED is most effective.

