##### Local routine data

We will obtain routine data about the number and characteristics of patients who have consulted primary and other urgent care services outside the emergency department, and any available information about other observable characteristics of the local health economy such as patient outcomes and satisfaction, adverse incidents and reports, to provide contextual data that will help us to interpret findings from the case study sites.

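### WP-B compares GPED models on a primary outcome of ED attendances with no measure of overall attendances, so separate registration of GP patients could look like reduced demand

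*Protocol article*

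**What the plan says.** Box 1 (Protocol article, WP-B, Methods) gives one primary outcome, the count of ED attendances, and six secondary outcomes. One of these is "Mortality within 28 days of attendance"; none is another attendance total. The WP-B Analysis section aims to "identify the causal effect of each GPED model on the primary and secondary WP-B outcomes", using interrupted time series and difference-in-difference models. It then stratifies by model to "determine whether there are differences in effects, and as such which model of GPED is most effective".

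Three other places bear on this:

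- **Models.** The Introduction describes three: a GP service beside the ED, a front-door filter with GPs "screening attendees and either treating or diverting to other places", and a fully joint operation.
- **Threat.** The Introduction also cautions: "Some of the apparent impact of GPED on emergency departments may simply be relabelling of the same work". It adds that co-located services may raise demand at the hospital site.
- **Objective.** Objective 2 in Table 1, assigned to WP-B and WP-C, covers "overall attendances, attendances in different components of the local urgent care system".

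In WP-C, the case-study sites supply local data on the "number and characteristics of patients who have consulted primary and other urgent care services outside the emergency department". These are described as contextual and are to be analysed mainly descriptively.

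**The concern.** The exposure can change what the primary outcome counts. If a patient who would have been booked into the ED is instead booked into a separate GP service at the same door, the ED count drops by one and arrivals do not change. If the GP works inside a joint operation with a single register, the same patient stays in the count. The models could then differ on the primary outcome through registration alone.

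Two conclusions are at stake. The first is the pooled effect of GPED on attendances. The second is the attendance part of the judgement on which model works best. The costs-and-consequences work draws on the estimated effects on the Box 1 outcomes, so an artefact would carry into it. With no overall count in WP-B, its causal models cannot distinguish fewer arrivals from the same arrivals under another label, or from more arrivals that the GP service absorbs.

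**Working it through.** The article gives no power, sample size or effect figure on this point, so there is none to reproduce. The check is a comparison of passages and an illustrative calculation.

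**Passages side by side.** Objective 2 asks for overall attendances and attendances by component of the urgent care system. Box 1 carries only the ED component. The Box 1 check on trusts' coding behaviour is attached to zero-day admission and not to the attendance count. The safeguard against cost shifting concerns which budget bears a cost.

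**Why the difference-in-difference does not help.** Let A be arrivals before GPED at a treated site and at its control, with a common proportional trend t. Let d be the share of would-be ED patients registered elsewhere once GPED starts.

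- Treated site, ED count after / before = A(1 + t)(1 − d) / A = (1 + t)(1 − d)
- Control site, ED count after / before = A(1 + t) / A = 1 + t
- Ratio of the two = 1 − d

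The trend cancels. The recording change does not, because it starts with GPED and only at the treated site.

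**Size of d.** d = s × f, where s is the share of ED patients a GP could manage and f is the fraction of them registered outside the ED. The Introduction says that estimates of s "vary widely between 15% and 40" per cent. The article does not give f, so a range is assumed.

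| s | f = 0 | f = 0.25 | f = 0.5 | f = 1 |
|---|---|---|---|---|
| 0.15 | 0% | −3.75% | −7.5% | −15% |
| 0.40 | 0% | −10% | −20% | −40% |

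Entries are the change in the ED count, −100 × s × f, with arrivals constant. The combined ED plus GP count changes by 0% in every cell. The f = 0 column is the case in which every GP-seen patient is still recorded as an ED attendance.

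**Sign.** Suppose GPED also draws 5% extra arrivals (an assumption), all registered by the GP service. The combined count is then 1.05A, or +5%, while the ED-only count is still A(1 − d). For f from 0.25 to 1, that is −3.75% to −40%.

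**Secondary outcomes.** If one is expressed per ED attendance, and the patients registered elsewhere have no such events (both assumptions), its rate is multiplied by 1 / (1 − d). With f = 1 this is 1 / 0.85 = 1.18 for s = 0.15 and 1 / 0.60 = 1.67 for s = 0.40. On that basis the secondary outcomes would not correct the comparison.

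**The case against.** A reader might infer that WP-B ranks the models on ED attendances alone. The article does not say so. The Analysis section covers primary and secondary outcomes, a cost analysis is planned, and no single outcome or rule is named for deciding which model is most effective.

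A reader might also infer that the ED count will fall as an artefact. That is not established. The article describes where GPs work and not how their patients are registered, and the full protocol or analysis plan, not shown here, may define the count. The effect arises only where GP-seen patients are not recorded as ED attendances.

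ED attendances are a legitimate target. The policy aims to relieve EDs, and real diversion by a filter is a real effect on ED workload. Only relabelling is an artefact. It would therefore go too far to say that the ED count is the wrong primary outcome or should be replaced.

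The plan also has partial safeguards: local data and observation in at least 10 case-study sites, a WP-A enquiry into configuration and start dates, scope to exclude hospitals on data quality, and an open statement that routine data are limited.

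All of this stands against the stronger readings. It does not close the gap. Contextual, mainly descriptive data from the case-study sites do not correct a national causal estimate, and the mismatch between objective 2 and Box 1 is visible in the article itself.

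**Conclusion.** The point holds in a conditional form. The only attendance outcome in the WP-B causal models is the ED count, the models under comparison differ in where patients are handled, and the protocol itself names relabelling as a possible explanation of apparent impact. A fall in the ED count cannot by itself be read as reduced demand, and a difference between models on that count cannot by itself be read as a difference in effectiveness.

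The size is unknown. The range of 3.75% to 40% combines a documented 15% to 40% with an assumed 25% to 100% registered elsewhere. The upper end needs every GP-manageable patient to be registered outside the ED. If all are registered in the ED, the artefact is zero. The figures show what could happen and do not estimate the likely bias.

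**What to change.** - **Outcome.** Keep the ED count as primary. Add to Box 1 and the WP-B Analysis section a companion outcome of all recorded front-door attendances (ED plus co-located GP service). Fit it in the same models and report the ED and GP counts as components.
- **Enquiry.** Add one item to the WP-A site enquiry: how GP-seen and diverted patients are registered, whether those contacts reach national data, and from what date.
- **Sensitivity.** Run the between-model attendance comparison with and without sites whose GP contacts are not in national data, and report how many are excluded under each model. Exclusion should not be the only analysis, because such sites may cluster by model.
- **Interpretation.** State in advance that a fall in the ED-only count will not be read as reduced demand unless the combined count also falls.
- **Case studies.** Use the WP-C local counts to show how large relabelling is where it can be observed.

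The cost is one enquiry item and one extra outcome. The combined count will be incomplete at some sites, possibly more under one model than another, and it will miss patients sent to services away from the front door. Both limits should be reported with the result.

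### WP-B ties the choice of the most effective GPED model to analyses stratified by model and names no direct contrast between models

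*Protocol article*

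**What the plan says.** The Research question section of the protocol article asks two things. The second is "What is the differential impact of alternative models of GPED".

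The opening of the WP-B section sets the comparator: "We will measure the impact of the GPED models identified in WP-A, compared with a no-GPED model". The design there is "difference-in-difference regression models with closely matched non-GPED sites as controls".

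The Analysis section of WP-B then gives the sequence:

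- A pooled step: "We will initially pool all hospitals and GPED types to identify levels and trends before and after implementation, using a multilevel approach".
- A look at timing: "Trends in each hospital and subgroup (based on date of service introduction) will be examined".
- A stratified step: "We will also conduct stratified analysis by GPED model and by early/late adopter status". Its stated purpose is "to determine whether there are differences in effects, and as such which model of GPED is most effective".

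The WP-A section expects two or three model types to be carried into WP-B. The article names no model-by-effect term, heterogeneity test, or interval for a difference between two models. It does not say whether the two stratifiers are crossed or used one at a time.

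**The concern.** The last clause of the Analysis section is an inference rule: the most effective model is to follow from the stratified results. Each stratum answers whether that model differs from no GPED. Whether one model differs from another is a separate question, with its own estimate and standard error. One model can show a clear effect and another an unclear one when the two true effects are the same.

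This bears on half of the research question. The Discussion says that the study should identify the models most likely to be efficient. The costs and consequences work in WP-B uses the same model-specific effects, so a model that leads by chance would also lead in the economic results.

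Adoption date is a second route to a false winner. If one model was mostly taken up early and another mostly late, and the effect of GPED differs between early and late adopters, a one-way split by model mixes the two influences.

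**Working it through.** **Inputs.** From the protocol article: k = 2 or 3 models, effects measured against matched no-GPED controls, and stratification by model and by early/late status. The article gives no significance level, power, effect size or number of hospitals per model for WP-B, so it has no figure to reproduce. Assumed for illustration: equal true effects in all models, two-sided 5% level, power p per stratum, equal standard errors, and correlation ρ between stratum estimates to represent shared controls.

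**1. What the contrast needs.** For stratum effects d_A and d_B with standard error SE, the difference d_A − d_B has standard error SE × √(2(1 − ρ)). With ρ = 0 it must reach 1.96 × √2 = 2.77 SE to be significant at 5%; with ρ = 0.5 it must reach 1.96 × √1 = 1.96 SE. Neither stratum's own test checks this.

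**2. Ranking by point estimate.** The average gap between the best and worst of k equal models was simulated (400,000 draws):

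| ρ | k = 2 | k = 3 |
|---|---|---|
| 0 | 1.13 SE | 1.69 SE |
| 0.5 | 0.80 SE | 1.20 SE |

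Some model always ranks first, and a visible gap is expected when nothing differs.

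**3. Judging strata by significance.** The protocol does not state this rule; it is one way the stratified results might be read. With independent strata, the chance that some are significant and others are not is 1 − p^k − (1 − p)^k.

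- p = 0.8, k = 2: 1 − 0.64 − 0.04 = 0.32.
- p = 0.8, k = 3: 1 − 0.512 − 0.008 = 0.48.
- p = 0.5, k = 2: 1 − 0.25 − 0.25 = 0.50.
- p = 0.5, k = 3: 1 − 0.125 − 0.125 = 0.75.
- p = 0.9: 0.18 (k = 2) and 0.27 (k = 3).

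Shared controls lower these figures. At p = 0.8, simulation with ρ = 0.3 gives 27% and 40%, and ρ = 0.5 gives 23% and 34%. Over p = 0.3, 0.5 and 0.8 with ρ = 0.5, the range is 23–33% for two models and 34–50% for three.

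**4. Direct test.** A heterogeneity test on k − 1 degrees of freedom gave a false-difference rate of 5% for both k at every ρ tried.

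**5. Adoption date.** With equal model effects and a one-way split, the spurious model gap is (difference in share of early adopters) × (early-minus-late effect). The shares and effect gaps below are assumed.

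- Shares 70% and 30%, effect gap 2 points: 0.4 × 2 = 0.8 points.
- Shares 60% and 40%, effect gap 1 point: 0.2 × 1 = 0.2 points.
- Shares 80% and 20%, effect gap 4 points: 0.6 × 4 = 2.4 points.
- Equal shares: 0, whatever the effect gap.

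**The case against.** The strongest reply is that the article is silent on the test and does not exclude one. Its stated aim includes finding out whether effects differ. Two stratum estimates can be subtracted, and their standard errors, with a covariance if controls are shared, give a valid contrast. A full analysis plan may do exactly that. This stands against any claim that the plan will never test the difference, or that it will compare p-values or pick the largest estimate. A reader might infer either, but the text says neither. It does not remove the point, because the article goes beyond silence: it states which analysis settles the choice of model, and that analysis is insufficient as described.

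A reader might also infer that adoption date and calendar time are ignored. They are not. Concurrent matched controls remove period shocks common to both groups, trends by date of introduction are examined, and early/late status is a stratifier. What remains is narrower: effects that vary by adoption cohort, if the two stratifiers are used one at a time or the early/late split is too coarse.

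Finally, a reader might take "There is no sampling for this WP, therefore, a sample size calculation is not appropriate" as a denial that precision matters. The documents do not support that reading. The number of hospitals is fixed in a retrospective national dataset, the sentence concerns choosing a sample size, and the counts per model were not known before WP-A.

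The objection that the percentages have no anchor in the article is correct. They are illustrations only.

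**Conclusion.** The point holds in limited form. The protocol rests the choice of the most effective model on stratified effects, each against no GPED, and names no direct between-model contrast for a question that it poses as one of its two. Those effects alone cannot carry that conclusion.

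The size of the problem cannot be computed from the article. That a ranking always produces a winner needs no assumption about power. The 32% and 48% figures need 80% power per stratum, independent strata and a reading by significance; shared controls reduce them but leave them well above 5%. The adoption-date bias depends on one-way stratification, on unequal early shares, and on an effect that differs between early and late adopters. The article settles none of these.

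**What to change.** In the Analysis section of WP-B, build the between-model comparison into the pooled multilevel analysis that is already planned:

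- Fit it as one difference-in-difference model with GPED-model-by-post terms, common period effects and adjustment for adoption cohort.
- Report a heterogeneity test across models, and pairwise differences between models with 95% CIs.
- State that a model will be called more effective than another only on such a contrast.
- Keep early versus late adoption as a separate question about effect modification.

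Stratum-specific effects against no GPED can still be reported as description. The cost is revised wording and one extra model on the same data. The downside is that the conclusion about which model to prefer may be less definite, because a difference between two models is usually estimated less precisely than either model's own effect.
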